## Abstract

**Background:**

Hypertension markedly increases the risk of cardiovascular diseases and overall mortality. Lifestyle modifications, such as increased levels of physical activity, are recommended as the first line of anti-hypertensive treatment. A recent systematic review showed that isometric handgrip (IHG) training was superior to traditional endurance and strength training in lowering resting systolic blood pressure (SBP). The average length of previous IHG training studies is approximately 7.5 weeks with the longest being 10 weeks. Therefore, presently it is unknown if it is possible to further lower blood pressure levels beyond the 10-week mark. Recently, we developed a novel method for monitoring handgrip intensity using a standard Nintendo Wii Board (Wii). The primary aim of this study is to explore the effects of a 20-week IHG home training facilitated by a Wii in hypertensive older adults (50 + years of age) on lowering SBP compared to usual care. Secondary aims are to explore if/when a leveling-off effect on SBP will occur during the 20-week intervention period in the training group and to explore adherence and potential harms related to the IHG home training.

**Methods/design:**

Based on previous evidence, we calculated that 50 hypertensive (SBP between 140 and 179 mmHg), older adults (50 + years of age) are needed to achieve a power of 80% or more. Participants will be randomly assigned to either an intervention >group (IHG home training + hypertension guidelines on lifestyle changes) or to a control group (hypertension guidelines on lifestyle changes). Participants in the intervention group will perform IHG home training (30% of maximum grip strength for a total of 8 min per day per hand) three times a week for 20 weeks. Resting blood pressure and maximal handgrip strength will be obtained by a blinded outcome assessor in both groups at specific time points (baseline, follow-up at 5, 10, 15, and 20 weeks) throughout the study.

**Discussion:**

This assessor-blinded, randomized controlled trial will explore the effect of a 20-week IHG home training intervention on resting blood pressure in hypertensive older adults. In addition, the trial will report adherence and potential harms related to the IHG home training.

**Trial registration:**

ClinicalTrials.gov, ID: NCT03069443. Registered on 3 March 2017.

**Electronic supplementary material:**

The online version of this article (doi:10.1186/s13063-018-2441-x) contains supplementary material, which is available to authorized users.

## Background

Hypertension (HT) is a major public health concern worldwide with an upward trend [1]. HT increases the risk of cardiovascular diseases (e.g., coronary artery disease, stroke, and heart failure) and overall mortality [2, 3]. Both European and US treatment guidelines for primary and secondary prevention of HT recommend non-pharmacological lifestyle modifications, such as increased levels of physical activity, as the first line of anti-hypertensive therapy [4, 5]. In addition, there is class I, level B evidence that 150 min of weekly physical activity offers an alternative that may be used to complement anti-hypertensive medication, although optimal exercise training regime remains unclear [6]. A systematic review from 2013 highlighted the potential of isometric handgrip (IHG) training regimens in reducing systolic blood pressure (SBP) [7]. The meta-analysis from the review showed that IHG training was superior to endurance training and dynamic resistance training in reducing SBP (by − 10.9, − 3.5, and − 1.8 mmHg, respectively) [7]. Another systematic review published in 2014 on IHG training, including isometric leg extension training, reported a more modest mean difference of − 6.77 mmHg in SBP [8]. Lately in 2016, yet another systematic review was published on isometric training (both handgrip and leg extension) and showed an overall reduction in SBP of − 5.2 mmHg [9]. This review, however, was heterogenetic in nature with several outlying studies, which may have undermined the effect of isometric training on blood pressure levels. In addition, some of the studies included in the most recent review were performed on normotensive populations and may have contributed to a reduced effect compared to the systematic review from 2013. Overall, most isometric exercise training studies have followed somewhat the same exercise protocol with an intensity of 30% of maximum voluntary contraction (MVC) in intervals of 2 min per hand/foot (a total of 8 min per hand/foot per day). In addition, the training has been three times per week for an average of 7.5 weeks in duration with the longest reported study being 10 weeks [9]. Most of the studies have been conducted at a hospital, university, or healthcare clinic burdening the participant by having to travel to the study site for assessment and training. Finally, many of the previous studies on IHG training have been relatively small in size (average 28 participants) [9].

Recently, we have shown that handgrip [10] and lower extremity strength [11] can be measured precisely using a standard Nintendo Wii Board (Wii) with an on-screen visual feedback of the force exerted over time (force/velocity curve). As a continuation of this work, we have further developed a novel method that monitors handgrip muscle control and is suitable for IHG home training. Given the development and low-cost nature of the Wii, we are now able to perform home-based IHG training. For the above reasons we intend to conduct a IHG training study, which will be twice as long (20 weeks) as the longest previous study (10 weeks) to explore the effects on specific measures of blood pressure and other relevant outcomes. Our primary aim is to explore the effects of 20 weeks’ IHG home training facilitated by a Wii in hypertensive older adults (50 + years of age) in lowering SBP. Secondary aims are to explore if/when a leveling-off effect on SBP will occur during the 20-week intervention period in the training group and to explore adherence and potential harms related to the IHG home training. The study will compare IHG home training with a control group in a randomized, assessor-blinded design. Thus, we hypothesize (1) that 20 weeks of IHG home training will significantly reduce SBP in hypertensive older men and women compared to usual care, (2) that a leveling-off effect on SBP will occur during the 20 weeks of IHG training, and (3) that a minimum of 50% of participants will complete at least 50% of their training sessions (30 sessions).

## Methods/design

### Design

The design of the study will be a randomized controlled, outcome-assessor-blinded superiority trial with participants randomly assigned to either an intervention group (IHG home training + hypertension guidelines on lifestyle changes) or to a control group (hypertension guidelines on lifestyle changes). The length of the study will be 20 weeks and the IHG training will be performed in the participant’s own home. Randomization will be made using a computer-generated block randomization with 1:1 allocation between the intervention group and the usual-care group (see Fig. 1). The protocol follows the Standard Protocol Items: Recommendations for Interventional Trials (SPIRIT) 2013 guidelines Additional file 1 [12].

**Fig. 1 Fig1:**
[figure not shown]
Flowchart of the POTENT study. *IHG* isometric handgrip training

### Participants and setting

The study will be conducted at one study site: Aalborg University Hospital, Department of Geriatric and Internal Medicine, Aalborg, Denmark. Participants will, therefore, primarily consist of individuals living in an urban environment. Using the criteria below, we attempt to target a study population which has a 15–20% or medium absolute risk of stroke or myocardial infarction within a 10-year period according to the Danish Hypertension Society [13]. Written informed consent will be obtained from each participant.

#### Inclusion criteria

Participants eligible for the POTENT study must comply with all of the following criteria prior to randomization:Age 50 + years oldHave a resting SBP between 135 and 179 mmHg and either taking no actual anti-hypertensive medicine or taking actual anti-hypertensive medicine with no treatment change within the last 4 months prior to enrollment

#### Exclusion criteria

Manifest cardiovascular disease (cerebrovascular disease, heart failure, chronic kidney disease, peripheral vascular disease, or advanced retinopathy (fundus hypertonicus grades III–IV))Diabetes (any type)More than three blood-pressure-regulating agentsPhysical limitation preventing IHG training (e.g., missing an arm or having a musculoskeletal disorder)Severe arthritis in the hand, or carpal tunnel syndromeA resting SBP ≥ 180 mmHg (will be advised to consult a physician)

### Sample size

Based on previous evidence [14], and using a more conservative approach, we carried out an a priori power analysis assuming a 7-mmHg difference in the ∆SBP between the IHG training and the usual-care group (favoring the IHG training group) after 20 weeks of training. In addition, we assumed the standard deviation of the IHG training and usual-care group to be 8 and 9 mmHg, respectively. We further choose a power of 80% and an alpha level of 5% with equal group sizes. This resulted in a total sample size of 40 participants with 20 in each group. Assuming a 25% loss to follow-up, we would need to recruit 25 participants in each group.

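### Twenty per group gives about 72–74% power at a two-sided 5% level, not 80%; the figure of 20 comes out only from an undeclared one-sided calculation

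*Protocol article*

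**What the plan says.** The Sample size section of the protocol article gives every input to the calculation. The target is a 7 mmHg difference in the change in SBP, in favour of training, after 20 weeks. On variability: "we assumed the standard deviation of the IHG training and usual-care group to be 8 and 9 mmHg, respectively". On error rates and allocation: "We further choose a power of 80% and an alpha level of 5% with equal group sizes". The result follows: "This resulted in a total sample size of 40 participants with 20 in each group". The section then raises the number to 25 per group for an assumed 25% loss to follow-up.

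The abstract (Methods/design) carries the result forward: it says that 50 participants "are needed to achieve a power of 80% or more".

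Sidedness is stated nowhere. The Design section describes a "randomized controlled, outcome-assessor-blinded superiority trial", and the Data analysis section names a linear mixed-effects model for the change from baseline to week 20. Neither says whether the primary test is one- or two-sided.

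**The concern.** A 5% alpha given without qualification in a superiority trial is normally read as two-sided. On that reading, 20 per group looks too few for a 7 mmHg difference with SDs of 8 and 9.

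Two things are at stake. If the primary test is two-sided, the power on which the trial is justified is not a property of the design, and a null result would be read against a power that it never had. If the primary test is instead run one-sided at 5% to match the calculation, the false-positive rate for claiming superiority is 5% rather than the conventional 2.5%, and readers are not told.

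**Working it through.** **Inputs** (all from the Sample size section): difference δ = 7 mmHg; SDs 8 and 9 mmHg; power 80% (z = 0.8416); alpha 5%; equal groups. The sum of the variances is 8² + 9² = 64 + 81 = 145, equivalent to a common SD of √(145/2) = 8.51.

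**Formula** (normal approximation): n per group = (z_α + 0.8416)² × 145 / 7².

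**Reproducing the plan's 20: one-sided 5%**
- z_α = 1.645: 6.183 × 145/49 = 18.3, so 19 per group.
- With the noncentral t, 19 per group gives just under 80% (79.98% equal-variance, 79.96% Welch) and 20 gives 81.8%. The t-test answer is therefore exactly 20.

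**Two-sided 5%**
- z_α = 1.960: 7.849 × 145/49 = 23.2, so 24 per group.
- With the Welch t test, 24 per group gives 79.6% and 25 gives 81.3%, so 25 are needed.
- The gap from the plan's figure is 4–5 per group, or 8–10 in total. That is too large to be rounding or the choice between the normal and t distributions.

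**Power at 20 analysed per group**
- Standard error of the difference = √(145/20) = 2.693; 7/2.693 = 2.60.
- Two-sided, normal: Φ(2.60 − 1.96) = Φ(0.64) = 73.9%. Noncentral t: 71.7%.
- One-sided, normal: Φ(2.60 − 1.645) = 83.0%. Noncentral t: 81.8%.

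**Difference detectable with 80% two-sided power at 20 per group**
- Normal: (1.960 + 0.8416) × 2.693 = 7.5 mmHg. By t: 7.7 mmHg. The plan assumes 7.

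**Could another two-sided reading of the SDs give 20?**

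| SD used in both arms | n per group, normal | n per group, t |
|---|---|---|
| 8 | 21 | 22 |
| 8.5 | 24 | 25 |
| 9 | 26 | 27 |

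None gives 20. The nearest, SD 8 in both arms, discards the stated SD of 9.

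**The abstract's 50 participants, two-sided**
- All 25 per group analysed: 82.8% (normal) or 81.3% (t).
- After the plan's own 25% loss: 25 × 0.75 = 18.75 per group, which gives about 71% (normal) or 69% (t).

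**The case against.** The strongest reply is that the document never says two-sided, and that under a one-sided 5% t test its figure is exact. The assumed difference and the first hypothesis in the Background are both worded in one direction. This is fair as far as it goes: the calculation may well have been one-sided. But directional wording is routine ahead of two-sided testing and does not declare a one-sided test. An undeclared one-sided 5% level would itself need correcting.

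A second reply is that the abstract's claim concerns 50 participants, and 25 analysed per group does exceed 80%. That requires no loss at all, whereas the plan adds the five extra per group precisely because it expects to lose 25%.

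A third is that the mixed model may be more efficient than a two-sample comparison, through baseline adjustment or the visits at weeks 5, 10 and 15, and that participants lost before week 20 may still contribute data. This is possible. By the normal approximation a variance reduction of about 14% would restore 80% at 20 per group (20/23.2 = 0.86); by the t test about 18%. Whether that is achieved depends on a correlation that the protocol does not give, and the calculation takes no credit for it. What stands is that the 72% is the power of a two-sample comparison on the plan's own inputs, not a forecast for the fitted model.

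**Conclusion.** The concern holds. On the protocol's own difference, SDs and allocation, 20 analysed per group gives 71.7% (t) to 73.9% (normal) power at a two-sided 5% level, a shortfall of about 6 to 8 percentage points. Reaching 80% needs 24–25 analysed per group. The stated 20 is reproduced only by a one-sided 5% calculation.

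The conclusion rests on reading the unqualified 5% as two-sided, and on a two-sample comparison of change scores, which is how the section frames its inputs. If one-sided testing was intended, the arithmetic is right, and the fault is an undisclosed significance level twice the usual one. On either reading the text must change, because it concerns the stated justification for the primary comparison and appears in both the abstract and the methods.

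**What to change.** 1. In Sample size, state that alpha is 0.05 two-sided and give the power as about 72% with 40 analysed participants (two-sample t test; difference 7 mmHg; SDs 8 and 9).
2. In the abstract, delete the claim that 50 participants give 80% power or more.
3. In Data analysis, state that the primary p-value and 95% confidence interval are two-sided.

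If the sponsor wants to claim more power from baseline adjustment or repeated measures, the calculation should be redone for that model, with the assumed correlation and retention stated.

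The cost is wording in a few places and a less favourable stated power. No extra recruitment is requested. For comparison, keeping 80% two-sided on the present inputs would mean recruiting 24/0.75 = 32 to 25/0.75 = 33.3, so 34, per group. The Trial status section says that recruitment has not yet begun, so the correction can be made before any data are seen.

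### The 25% loss allowance is computed as 20 × 1.25 rather than 20 / 0.75, so 25 recruits per group cover a 20% loss, not the 25% stated; the effect on power is small

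*Protocol article*

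**What the plan says.** The Sample size section of the protocol article sets out its inputs in sequence. The effect is fixed by "assuming a 7-mmHg difference in the ∆SBP between the IHG training and the usual-care group", and the variability by the sentence "we assumed the standard deviation of the IHG training and usual-care group to be 8 and 9 mmHg, respectively". The error rates follow: "We further choose a power of 80% and an alpha level of 5% with equal group sizes". The result is given as "This resulted in a total sample size of 40 participants with 20 in each group". The allowance for attrition comes last: "Assuming a 25% loss to follow-up, we would need to recruit 25 participants in each group".

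The abstract (Methods/design) carries the recruitment total forward, saying that 50 hypertensive older adults "are needed to achieve a power of 80% or more". The Design section confirms 1:1 allocation, so 50 means 25 per group. Nothing in the article gives the 25% any meaning other than the share of participants lost to follow-up.

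**The concern.** The section prints three numbers that should be linked by one line of arithmetic: 20 needed, 25% lost, 25 recruited. Loss to follow-up is a fraction of those recruited, so the number recruited times 0.75 should return at least 20. It does not.

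If the loss turns out as assumed, the trial ends with fewer analysable participants than its own calculation requires, and the abstract's assurance of at least 80% power no longer follows from the figures given. The shortfall can be removed on paper, and according to the Trial status section recruitment had not begun when the article was written.

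**Working it through.** **Inputs (all from the Sample size section).** Difference in change in SBP 7 mmHg; SDs 8 and 9 mmHg; power 80%; alpha 5%, sidedness not stated; equal groups; 25% loss.

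**Step 1: reproduce the plan's 20 per group.**

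- Common SD = √((8² + 9²)/2) = √72.5 = 8.51 mmHg.
- One-sided 5% two-sample t-test at 80% power: n = 19.01, rounded up to 20 per group. This matches the plan.
- One-sided normal approximation: n = 18.3, so 19 per group.
- Two-sided 5%: n = 23.2 (normal), so 24; or 24.2 (t-test), so 25 per group. Neither matches.

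The stated 20 is therefore reproduced on a one-sided basis only.

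**Step 2: the attrition step.**

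- The plan's 25 equals 20 × (1 + 0.25) = 25.
- The correct inflation is 20 / (1 − 0.25) = 26.7, so 27 per group, 54 in total.
- Check on the stated target: 25 × 0.75 = 18.75 per group; 50 × 0.75 = 37.5 in total.
- Check on the corrected target: 27 × 0.75 = 20.25 per group.
- Loss that 25 per group actually tolerates: 1 − 20/25 = 20%.

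Rounding cannot explain the difference, because 26.7 does not round to 25.

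**Step 3: what the shortfall costs in power.** The standardised effect is 7 / (8.51 × √(2/n)), which is 2.60 at n = 20 and 2.52 at n = 18.75.

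| Analysable per group | One-sided 5%, t | One-sided 5%, normal | Two-sided 5%, t | Two-sided 5%, normal |
|---|---|---|---|---|
| 20 | 81.8% | 83.0% | 71.7% | 73.9% |
| 19 | 79.98% | 81.3% | 69.4% | 71.7% |
| 18.75 | 79.5% | 80.8% | 68.7% | 71.1% |
| 25 (no loss) | 88.9% | 89.6% | 81.3% | 82.8% |

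Using the t-test columns, moving from 20 to 18.75 per group costs 81.8 − 79.5 = 2.3 points one-sided and 71.7 − 68.7 = 3.0 points two-sided.

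**The case against.** The arithmetic itself is hard to dispute. The case on the other side is about size, and most of it stands.

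- **The effect on the plan's own basis is slight.** The one-sided t-test needs 19.01 per group, so an expected 18.75 is about a quarter of a participant short. With the normal approximation, one-sided power at 18.75 is 80.8%, still above 80%. This stands.
- **A reader might infer that the attrition slip brings power down to about 69%.** The figures do not support that. Two-sided power is already 71.7% at the plan's own 20 per group, before any loss is considered. The slip accounts for about 3 points; the remaining 80 − 71.7 = 8.3 points arise because 20 is too few for a two-sided test, and the article does not state the sidedness.
- **A reader might also infer that the slip alone makes the abstract's claim of 80% power or more plainly false.** That is too strong. With all 50 analysed, power is 81.3% two-sided and 88.9% one-sided. The claim fails only if the full 25% is lost and those participants contribute nothing. One-sided, it then fails by 0.5 points (t-test) or not at all (normal).
- **The planned analysis may recover some information.** The Data analysis section specifies intention to treat and a linear mixed-effects model, and there are visits at weeks 5, 10 and 15, so participants who leave before week 20 may still contribute. This is fair mitigation. However, the sample-size calculation does not invoke it, and it does not make 25 × 0.75 equal 20.

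**Conclusion.** The point holds as a minor arithmetic error. At the stated 25% loss, 25 recruits per group leave 18.75 rather than 20; the number consistent with that loss is 27 per group (54 in total), four more than planned. The cost is 2 to 3 percentage points of power: from 81.8% to 79.5% on the one-sided basis that reproduces the plan's 20, or from 71.7% to 68.7% two-sided.

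These powers assume the stated 7 mmHg difference and SDs of 8 and 9, a two-sample t-test on the change at 20 weeks, exactly 25% loss in each group, and no contribution from those lost. The design, endpoint and analysis are unaffected. The error does not explain most of the two-sided shortfall from 80%, and correcting it would not remove that shortfall: 27 per group restores about 20 analysable per group and hence only about 72% two-sided power.

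**What to change.** Keep the target at 50 and correct the wording in the Sample size section. State that 25 per group tolerates a 20% loss, that about 19 per group would remain at a 25% loss, and what the power would then be on the sidedness actually used (79.5% one-sided or 68.7% two-sided, by the t-test at 18.75 per group). Naming the sidedness is necessary for that sentence, but the choice itself should be made on its own grounds and not through this correction. Qualify the abstract's power statement in the same way. The cost is wording only.

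If the sponsor prefers to keep the 25% loss assumption and the 20 per group, the recruitment figure should read 27 per group, 54 in total, in both places. That costs four more participants.

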### Recruitment and randomization procedure

Participants will be recruited consecutively by their local physician, through bulletin, newspaper advertisement, local senior citizens’ centers, and health/activity clubs. Eligible subjects, who agree to participate, will be asked to provide an informed written consent, undergo baseline assessment, and will thereafter be randomized to one of the two arms: (1) IHG training or (2) usual care. Participants will randomly be assigned by computer-generated random numbers in permuted blocks to attend either arm for 20 weeks. The randomization will be stratified according to gender (male/female). A third party not involved in the day-to-day running of the study will perform group allocation and will notify the study coordinator by e-mail to ensure concealed allocation.

### IHG training group and usual-care group

Participants of the intervention group will follow the home-based IHG training protocol for 20 weeks. The IHG training consists of isometric contractions applied with the hands on a Wii. The Wii will be connected to a standard PC to monitor the level of the applied force using the FysioMeter software (Brønderslev, Denmark). The IHG training will be structured with four sets of 2-min contractions for each hand, 3 days per week for 20 weeks. The training volumes will this way sum up to a total of 480 min for each hand in the study period. The level of IHG training will be set to 30% MVC in line with previous IHG training trials [7, 9]. During training sessions, participants will be seated on a standard chair with the non-working hand holding on to the Wii at the middle of the board, while the working hand will grab the corner of the Wii (see Fig. 2). Participants will alternate between the left and right hand with a 1-min resting period between changing hands. The software displays the target force level (30% MVC) on-screen as a horizontal line (yellow line, see Fig. 2) and participants will apply the required force level on the Wii according to this line (black line, see Fig. 2). Participants will be asked to do the IHG training every other weekday (i.e., Monday, Wednesday, and Friday) allowing for restitution between training days.

